## Abstract

**Background:**

Amnesic mild cognitive impairment (aMCI) is the main subtype of mild cognitive impairment (MCI) and has the highest risk of conversion to Alzheimer’s disease (AD) among all MCI subtypes. Episodic memory impairment is the early cognitive impairment of aMCI, which has become an important target for AD prevention. Previous clinical evidence has shown that acupuncture can improve the cognitive ability of MCI patients. This experiment aimed to observe the efficacy and neural mechanism of *TiaoshenYizhi* acupuncture on the episodic memory of patients with aMCI.

**Methods:**

In this multicenter, parallel-group, double-blind, randomized controlled trial, 360 aMCI participants will be recruited from six subcenters and randomly assigned to the acupuncture group, sham acupuncture group, and control group. The acupuncture group will receive *TiaoshenYizhi* (TSYZ) acupuncture, the sham acupuncture group will use streitberger sham acupuncture, and the control group will only receive free health education. Participants in the two acupuncture groups will receive real acupuncture treatment or placebo acupuncture three times per week, 24 sessions over 8 consecutive weeks. The primary outcome will be global cognitive ability. Secondary outcomes will be a specific cognitive domain, including episodic memory and execution ability, electroencephalogram, and functional magnetic resonance imaging data. Outcomes will be measured at baseline and the fourth and eighth weeks after randomization. Repeated measurement analysis of variance and a mixed linear model will be used to observe the intervention effect.

**Discussion:**

The protocol will give a detailed procedure to the multicenter clinical trial to further evaluate the efficacy and neural mechanism of *TiaoshenYizhi* acupuncture on episodic memory in patients with aMCI. From this research, we expect to provide clinical evidence for early aMCI management.

**Trial registration:**

http://www.chictr.org.cn/edit.aspx?pid=142612&htm=4, identifier: ChiCTR2100054009.

**Supplementary Information:**

The online version contains supplementary material available at 10.1186/s12906-023-04059-9.

## Background

Mild cognitive impairment (MCI) is the precursor stage of Alzheimer’s disease (AD), mainly manifested as memory or cognitive impairment that has no significant effect on daily ability [1]. The latest epidemiological survey results have shown that 38.77 million people aged 60 years and above in China suffer from MCI [2]. Among all subtypes of MCI, amnesic MCI (aMCI) has become a research hotspot because of its high incidence rate, high prevalence, and high conversion rate to AD. A meta-analysis of 41 studies on Chinese community-dwelling populations over 55 years of age has reported that the pooled prevalence of MCI was 12.2% for MCI and 10.9% for aMCI [3]. In a recent random sampling survey of 3246 community-dwelling older people in China, the prevalence of aMCI has been 17.1%, with an annual incidence rate of 70.57% [4]. Although MCI is a transitional state between normal aging and AD, its prognosis may have different outcomes due to its heterogeneity [5]. Studies have shown that the AD conversion rate is higher in aMCI than in the non-amnestic type, and aMCI is the subtype of MCI predominantly progressing to AD [6–8]. Therefore, it is of great significance to explore the early treatment of aMCI.

As a commonly used and safe complementary and alternative therapy, acupuncture has been demonstrated to be potentially effective in improving cognitive function in patients with MCI and dementia [9–15]. However, many existing studies have not distinguished non-amnestic MCI from aMCI. The symptoms of aMCI primarily comprise a decline in memory function with other cognitive domains remaining relatively intact, while the non-amnestic MCI does not cause memory impairment as the first symptom and prominent feature [8, 16, 17]. There are some specific biomarkers for the early diagnosis of aMCI and AD, such as β-amyloid and tau, but these measurements in clinical screening are invasive and expensive [18]. Episodic memory-associated neuropsychological scale screening is mature and inexpensive. Episodic memory impairment is the earliest and core manifestation of AD and a landmark clinical symptom of aMCI [19–23]. More evidence is needed to determine in what way and to what extent acupuncture could influence the episodic memory of patients with aMCI.

Most of the research on acupuncture treatment of MCI has focused on general cognitive function. There are many indexes in Mini-mental State Examination (MMSE), Montreal Cognitive Assessment Scale (MoCA), and Behavioral Observation Scales (BOS), which are closely related to episodic memory [23, 24]. These studies have also shown that acupuncture might have a positive effect on episodic memory, but there is a lack of special evaluation of episodic memory; thus, the research has not been in-depth. Therefore, it is extremely significant to investigate acupuncture intervention for the early episodic memory disorder of patients with aMCI.

### Objectives

The main purpose of this multicenter study is to verify the efficacy and safety of acupuncture treatment for episodic memory impairment in patients with aMCI through a randomized controlled trial and then explore its neuroimaging mechanism through functional magnetic resonance imaging (fMRI) and electroencephalogram (EEG).

## Methods and analysis

### Study design

The design of this study is a randomized controlled trial, strictly following the Standard Protocol Items: Recommendations for Interventional Trials (SPIRIT) statement (see Additional file 1) [25]. The allocation will be hidden, and the allocation ratio will be 1:1:1. A total of 360 eligible participants will be randomly assigned to the TiaoshenYizhi acupuncture group, the sham acupuncture group, and the control group. Participants will be evaluated at baseline (weeks -2 to 0) and weeks four, eight, and 12. EEG will be used to explore the diagnostic value of event-related potential (ERP) in aMCI, and fMRI will be used to measure the structure and function of brain regions related to episodic memory at baseline and eight weeks. All data collectors will not know the group assignment. The research procedure and results evaluation schedule of this trial are shown in Fig. 1 and Table 1.

**Fig. 1 Fig1:**
[figure not shown]
Flow chart of the study

**Table 1 Tab1:** Location of acupoints

Acupoints	Locations	Insert depth
Sishencong (EX-HN1)	On the vertex, 1 cun from the front, back, left, and right to GV20, common 4 points	0.5 cun
Yintang (EX-HN3)	At the forehead, at the midpoint between the two medial ends of the eyebrow	0.5 cun
Neiguan (PC6) (bilateral)	On the palmar aspect of the forearm, 2 cun above the transverse crease of the wrist, on the line connecting PC3 and PC7, between the tendons of m. palmaris longus and m. flexor carpi radialis	1.0 cun
Fenglong (ST40) (bilateral)	On the anterior aspect of the lower leg, 8 cun superior to the external malleolus, lateral to ST38, two fifinger-breadth (middle fifinger) from the anterior crest of the tibia	1.5 cun
Sanyinjiao (SP6) (bilateral)	On the medial side of the shank, 3 cun above the medial malleolus, by the posterior of the tibia	1.5 cun
Taixi (KI3) (bilateral)	On the medial border of the foot.posterior to the medial malleolus, in the depression between the tip of the medial malleolus and Achilles tendon	0.5 cun
Taichong (LR3) (bilateral)	On the dorsum of the foot, in the depression proximal to the fifirst metatarsal space	0.5 cun

### Study population

The study population will be community-based aMCI patients in Shenzhen, Fuzhou, Nanning, Nanjing, Bengbu, and Jiujiang city. The diagnostic, inclusion, and exclusion criteria of the study sample are as follows.

### Eligibility

#### Diagnostic criteria

The diagnostic criteria refer to the 2003 International Working Group’s diagnostic criteria for MCI recommended by the 2018 Chinese guidelines for the diagnosis and treatment of dementia and cognitive impairment, and the aMCI subtype will be determined based on these criteria [17, 26].

#### Inclusion criteria

The eligible participants must meet the following criteria:

Participants meeting the diagnostic criteria of aMCI.Participants aged 55–75 years.The participants’ mother tongue will be Chinese, and they will have at least a primary school education.Participants will be right-handed.Participants who have subjectively ongoing memory decline or cognitive decline compared to their normal status within the last five years, as confirmed by their caregivers.Participants whose ability of daily living (ADL) remained normal with ADL scale (14-item table) scores being ≤ 18 points.Participants participate voluntarily and provide signed informed consent.

#### Exclusion criteria

The following exclusion criteria will be used.

People with metal residues and tattoos on the body.People afraid of fMRI or those who cannot be scanned by fMRI for other reasons.People with identified or suspected brain lesions.People with a history of heavy drinking and drug abuse.People with a history of mental illness or congenital mental retardation; people who are taking anti-anxiety or anti-depression drugs and have been receiving psychological treatment in the past three months.People with serious heart, liver, and kidney diseases.People with other diseases of the nervous system that can cause cognitive dysfunction, such as brain tumors, encephalitis, epilepsy, Parkinson’s disease, etc.

### Recruitment

Participants will be recruited from the community of the six centers through WeChat ads, flyers, posters, volunteer recommendations, and community publicity. Potential eligible individuals will first complete the screening of community doctors in the community health service center, and their qualifications will be determined according to the inclusion and exclusion criteria. Qualified personnel interested in participating in the study will have an informed discussion with trained research assistants. The research assistant will obtain written informed consent from individuals willing to participate before the baseline assessment.

### Randomization, allocation concealment, and blinding

After baseline evaluation, the eligible participants will be randomly divided into the TiaoshenYizhi acupuncture group, sham acupuncture group, and control group. The randomly assigned sequences will be generated using the online randomization tool MedSci (http://tools.medsci.cn/rand) and managed by independent statisticians who are not involved in the recruitment, evaluation, and intervention of participants. The independent research assistant will inform eligible participants of their allocation results by telephone. We could not establish the blinding of participants, acupuncturists, or intervention supervisors to the assigned treatment, but result evaluators and data statisticians will be blind to the grouping assignment.

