The characteristics of acupuncture treatment make it difficult to implement the double-blind method; therefore, we will blind participants by setting up the sham acupuncture group as a placebo [28, 50]. Considering the placebo effect of sham acupuncture, the health education group will be set up as a negative control group, providing prevention knowledge of common geriatric diseases, including AD. We increased the sample size and expanded the scope of the crowd compared with our previous research. The intervention can be implemented in community medical centers, and the adverse events can be fully evaluated. The main challenge of this study is whether such a large number of patients with aMCI are willing to receive acupuncture treatment until the end of the study and cooperate with the collection of each outcome. We will give material rewards to the participants.

In conclusion, through this study, the effectiveness of TiaoshenYizhi acupuncture on the episodic memory of patients with aMCI will be further clarified. We expect that this study will provide a reference for early treatment of aMCI and AD. The results of the study will be reported according to the guidance of the Consolidated Standards of Reporting Trials statement (STRICTA) [51].

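### The plan contradicts itself on whether participants are blinded; if allocation is telephoned as written, the sham arm could lose its control of expectation

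*Protocol article*

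**What the plan says.** Four places in the protocol article bear on blinding.

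- **Abstract, Methods.** The trial is called a "multicenter, parallel-group, double-blind, randomized controlled trial".
- **Randomization, allocation concealment, and blinding.** After naming the three groups, the section says "The independent research assistant will inform eligible participants of their allocation results by telephone". The next sentence begins "We could not establish the blinding of participants, acupuncturists, or intervention supervisors to the assigned treatment" and ends by saying that "result evaluators and data statisticians will be blind to the grouping assignment".
- **Study design.** "All data collectors will not know the group assignment", which agrees with the blinded evaluators above.
- **Discussion.** "The characteristics of acupuncture treatment make it difficult to implement the double-blind method", and the answer offered is that "we will blind participants by setting up the sham acupuncture group as a placebo".

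The section on the sham acupuncture group describes a blunt, retracting Streitberger needle. It is applied at the same acupoints as real treatment, with angulation, duration of manipulation and apparent needle shortening made to match. The third arm receives health education and no needling.

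**The concern.** Real versus sham needling is the only comparison in this design that can separate the effect of needling from what a patient expects of it. The education arm has no needling and cannot do so. That separation depends on participants in the two needling arms not knowing which needle they receive. The section that governs conduct says they are not blinded and are told their allocation.

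If sham participants know they have sham, expectation could differ between the two needling arms. So could effort on the cognitive tests, willingness to stay in the trial and use of other treatments. Participants who know their arm could also reveal it to assessors. These are risks, not documented facts. They fall on the primary outcome (MoCA) and on AVLT-H, both of which depend on effort, and on SF-36, which participants report themselves. Up to 120 + 120 = 240 of the 360 planned participants are in this comparison.

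**Working it through.** The finding rests on comparing the text, and no stated figure needs to be reproduced.

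**Step 1. Set the statements side by side.**

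| Place | Participants | Evaluators, statisticians |
|---|---|---|
| Abstract, Methods | Blinded, on the usual sense of the label | Not stated |
| Randomization section | Not blinded; told allocation by telephone | Blinded |
| Discussion | Blinded by means of the sham | Not stated |

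The randomization section and the Discussion conflict directly on participants in the needling arms.

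**Step 2. Can the label be rescued?** One could read double-blind as evaluators plus statisticians. The Discussion tells against this. It says double-blinding is difficult and gives participant blinding through the sham as the response, so masking of participants is part of what the authors mean.

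**Step 3. Can the randomization section be read as referring only to the education arm?** Its wording covers participants without restriction. No section says the call reveals only needling or education. The matched sham procedure suggests that masking between the needle arms was intended, but six centres could act differently on the text as it stands.

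**Step 4. What would disclosure remove?** Both needle arms have 24 sessions over 8 weeks at the same acupoints. Contact, site and ritual therefore stay matched even if the arm is known. Expectation does not.

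**Step 5. Sense of scale, under an assumption.** The article gives no estimate of expectancy bias. Suppose that there is no true effect and that knowing the arm shifts the mean MoCA change by *b* points. Inputs from the Sample size section:

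- SDs of change: 2.48 and 2.45
- Analysed per arm: 300 / 3 = 100
- Two-sided alpha: 0.05

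Formulas (normal approximation):

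- Pooled SD = √((2.48² + 2.45²) / 2) = 2.465
- SE of the difference = 2.465 × √(2/100) = 0.349
- Rejection probability = Φ(b/SE − 1.96) + Φ(−b/SE − 1.96)

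| Assumed shift *b* (MoCA points) | Chance of rejecting |
|---|---|
| 0 | 5% |
| 0.1 | 6% |
| 0.2 | 9% |
| 0.3 | 14% |
| 0.4 | 21% |
| 0.62 | 43% |

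The last row uses the planning difference, 5.50 − 4.88 = 0.62 points. That difference is against a control group that the Sample size section does not describe, so it is a yardstick and not a planned real-versus-sham effect. The table shows only that a fraction of a point would matter. It does not estimate the bias.

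**The case against.** The best case for the plan has four parts.

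1. **The content of the call is not given.** That participants are told which of three groups they are in is an inference from adjoining sentences. The remark that participants could not be blinded may describe the three-arm trial as a whole, since the education arm cannot be masked. This stands in part. A reader might infer that the sham has failed, but the article shows an unreconciled contradiction, not an established failure. The harm is conditional on the text being followed as written.
2. **An unmasked sham still does something.** This stands. A reader might conclude that the retracting needle would control nothing, but contact, acupoints and ritual remain matched. Only control of expectation is lost.
3. **Evaluators, data collectors and statisticians are blinded, and MoCA is a scored test.** This reduces rating bias. It does not remove effects of expectation on a participant's effort, or on self-reported SF-36. A reader might infer that no result could be attributed to acupuncture. That goes too far, because both the size and the presence of bias are unknown.
4. **A changed call does not guarantee masking.** Real needling seeks De qi, while the sham is described as giving a pinprick-like sensation, so some participants may guess. This is true, but it is no reason to tell them.

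None of this reconciles the three statements.

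**Conclusion.** The concern holds as an internal contradiction with a conditional consequence. The abstract, the randomization section and the Discussion cannot all be true of participants in the needling arms, and no section resolves the conflict. If the randomization section is carried out as written, sham participants could learn their arm. The real-versus-sham comparison would then lose control of expectation, with possible bias on MoCA, AVLT-H and SF-36. The amount cannot be estimated from the article, and the rejection rates above rest on assumed shifts. The point needs correction because the interpretation of the sham comparison depends on what participants are told.

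**What to change.** 1. **Telephone call.** Disclose only needling or health education. Keep real versus sham masked to participants until after the week-12 visit.
2. **Blinding statement.** Rewrite the randomization section and the Discussion so that both state who is blinded for each comparison. For real versus sham: participants, assessors and statisticians. For either needle arm versus education: assessors and statisticians only. Acupuncturists are unblinded throughout.
3. **Label.** Replace double-blind in the abstract with that description.
4. **Participants already enrolled.** Record what each was told. If allocation was disclosed, add a sensitivity analysis restricted, in all arms, to those enrolled after the change. Do not simply drop those told they had sham. That is a one-sided exclusion after randomization, and it could remove every sham participant enrolled so far.
5. **Optional.** Ask participants in the needle arms at week 8 which treatment they think they received.

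The cost is a changed script, corrected wording, a check that the consent text agrees, a record of past disclosures and, if needed, one extra analysis. The Trial status section reports 37 participants recruited by 12 August 2022, which is 37 / 360 = 10% of the target. At that date, 360 − 37 = 323 participants could still have been enrolled under the corrected procedure; the number is smaller the later the change is made.

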### Interventions

#### TSYZ acupuncture group

Patients allocated to the TiaoshenYizhi (TSYZ) acupuncture group will take treatment with needles inserted at the prespecified acupuncture points. The acupoints include Sishenchong (EX-HN1), Yintang (EX-HN3), Neiguan (PC6), Fenglong (ST40), bilateral Sanyinjiao (SP6), Taixi (KI3), and Taichong (LR3). All acupoints are localized according to the WHO Standard Acupuncture Locations and exhibited in Fig. 2 and Table 1. Manipulations of twirling, lifting, and thrusting will be performed on all needles for at least 30 s to reach De qi (a compositional sensation including soreness, numbness, distention, and heaviness), which is believed to be an essential component for acupuncture efficacy [27].

**Fig. 2 Fig2:**
[figure not shown]
Location of acupoints

#### Sham acupuncture group

The streitberger sham acupuncture method will be used [28]. The acupuncturist will use a placebo needle in the sham acupuncture group. This placebo needle is not fixed inside the handle, and its tip is blunt. When the blunt needle touches the skin, a pinprick-like sensation will be felt by the person, while the needle is actually retracted into the handle without penetrating the skin and appears to be shortened (Fig. 3).

**Fig. 3 Fig3:**
[figure not shown]
Diagram of the streitberger sham acupuncture. 1. Needle handle. 2. Needle. 3. The blunt tip of the placebo needle. 4. Plastic cover. 5. Skin

The same acupoints as those in the TiaoshenYizhi acupuncture group are selected for placebo needle stimulation to avoid a site-specific effect of acupuncture. The angulation, duration of acupuncture manipulation, and the shortening of the needle will also appear the same as in the TSYZ acupuncture group.

#### Control group

The participants in control group will receive health education with a frequency of one session every 4 weeks (40 min per session) like the acupuncture groups.

### Outcome assessment

The variables in this trial consist of demographics and clinical characteristics, primary outcomes, and secondary outcomes. The basic characteristics will be measured at baseline (1–2 weeks before randomized allocation). Primary and secondary outcomes will be measured at baseline, the middle of intervention (4 weeks), the end of intervention (8 weeks), and 4 weeks of follow-up. Outcomes of fMRI and EEG will be measured at baseline and the end of intervention (8 weeks). All outcomes will be evaluated by experienced doctors who will be blinded to the allocation results of participants. A summary of all measurements in this trial is shown in Table 2.

**Table 2 Tab2:** Trial processes chart

Study period Item	Enrolment and Baseline	Intervention Period (8 weeks, one time per 4 weeks)				Follow-up phase
**Week**	-2 to 0	1 to 3	4	5 to 7	8	12
**Enrolment**						
Inclusion criteria	×					
Exclusion criteria	×					
Informed consent	×					
**Intervention**						
TSYZ acupuncture group		×	×	×	×	
Sham acupuncture group		×	×	×	×	
Blank control group						
**Outcome measurement**						
GDS	×					
BDI	×					
MoCA	×		×		×	×
AVLT	×		×		×	×
TMT	×		×		×	×
DSST	×		×		×	×
SF-36	×		×		×	×
fMRI scan	×				×	
EEG	×				×	
**Safety**						
Adverse events		×	×	×	×	×
Reasons for dropout and withdrawals		×	×	×	×	

*TSYZ* Tiaoshenyizhi, *GDS* Global Deterioration Scale, *BDI* Beck Depression Inventory, *MoCA* Montreal Cognitive Assessment, *AVLT-H* Auditory Verbal Learning Test-Huashan version, *TMT* Trail Making Test, *DSST* Digit Span Subtest, *SF-36* Medical Outcomes Study 36-item short form health survey, *EEG* Electroencephalogram, *fMRI* Functional magnetic resonance imaging

